#### Secondary outcome

To evaluate the between group difference in course in IKDC scores over the follow-up period, as indicated by the interaction between time point and randomized allocation, we will use mixed models. The IKDC score (at baseline and after 3, 6, 12 and 24 months of follow-up) will be used as a dependent variable. The randomized allocation will be used as an independent variable. Follow-up period and the interaction between follow-up and randomized allocation will be entered into the model as fixed factors.

Difference between groups in knee pain, kinesiophobia, shared decision making for patients and quality of life will be used as secondary outcomes. The analyses will be performed by using linear or binary mixed models for repeated measures. Return to pre-injury sport level, satisfaction with treatment and adverse events will be reported as comparative frequencies. Because of the potential for type 1 error due to multiple comparisons, findings for analyses of secondary endpoints should be interpreted as exploratory.

Difference between groups in shared decision making for physicians will be analyzed qualitatively, using the transcripts of the interviews’/focus groups’ audio files. The coding process will result in themes and patterns of shared meaning, underpinned or united by a central concept which are important for our research question [19].

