### Objectives

The aim of the current project is to evaluate the effectiveness and cost-effectiveness of the treatment algorithm for patients with a complete primary ACL rupture compared to current used treatment strategy. We hypothesize that the treatment algorithm will lead to earlier identification of the optimal treatment for the individual patient. We expect that fewer patients will receive a surgical reconstruction compared to the current practice and that fewer patients will need delayed surgery after non-operative treatment has failed. Hence, we hypothesize that with the treatment algorithm faster recovery of functional outcome will be achieved compared to the current practice (superiority study). As secondary outcome we expect that a faster recovery of functional outcome will lead to a faster return to work and sports. Hence, we hypothesize that the treatment algorithm will lead to lower societal cost. The treatment algorithm provides extra information for the physician and as well for the patient, to include in their decision for a(n) (non-)operative treatment. Therefore we expect the treatment algorithm will impact the shared decision making communication process.

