#### Primary objective

Assessing whether the treatment algorithm for patients with a complete primary ACL rupture is superior to the current practice regarding recovery of functional outcome at two-year follow-up.

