#### Secondary objectives

Assessing whether the treatment algorithm for patients with a complete primary ACL rupture is superior to the current practice regarding recovery of functional outcome during two-year follow-up.Assessing whether this treatment algorithm will increase the cost-effectiveness compared to the current practice.Assessing whether this treatment algorithm will lead to less ACL reconstructions compared to the current practice.Assessing whether this treatment algorithm will extend the (perception of) shared decision making during a physician-patient consultation.

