### Secondary outcomes

At baseline we will collect the following baseline characteristics, age, sex, height, weight, educational level, smoking habit, side affected and date and kinetics of trauma. Patient-rated outcome measures (PROMs) will be sent online at baseline, 3, 6, 12 and 24 months. There is an overview of all PROMs per follow-up moment in Table 1.

**Table 1 Tab1:** Patient-rated outcome measures (PROM) per follow-up moment

*PROMs*	*Baseline/1st consult*	*3 months*	*6 months*	*12 months*	*24 months*
*IKDC - subjective*	*x*	*x*	*x*	*x*	*x*
*Tegner*	*x*	*x*	*x*	*x*	*x*
*KOOS*	*x*				*x*
*Lysholm*	*x*	*x*	*x*	*x*	*x*
*NRS*	*x*	*x*	*x*	*x*	*x*
*Tampa scale*	*x*			*x*	*x*
*EQ-5D-5L*	*x*	*x*	*x*	*x*	*x*
*SDM-Q-9*	*x*				
*iMCQ/iPCQ*		*x*	*x*	*x*	*x*

*PROM* patient-rated outcome measures, *IKDC* International Knee Documentation Committee, *KOOS* Knee injury and Osteoarthritis Outcome Score, *NRS* number rating scale, *EQ-5D-5L* EuroQol 5D, *SDM-Q-9* 9-ltem Shared Decision Making Questionnaire, *iMCQ* Medical

We will measure the patients’ perception of symptoms, knee function and ability to participate in sports activities at 3, 6 and 12 months follow-up with the IKDC questionnaire. As mentioned above, the 24 month follow-up will be our primary outcome. Work and sports activities will be measured with the Tegner questionnaire (range 0–10; highest activity score is 10) at baseline, 3, 6, 12 and 24 months [12]. The Knee injury and Osteoarthritis Outcome Score (KOOS) will be assessed at baseline and 24 months of the subscales pain, symptoms, ADL, sports and quality of life (QoL) (range 0–100; optimal score is 100) [13]. Knee instability will be measured with the Lysholm questionnaire (range 0–100; optimal score is 100) at baseline, 3, 6, 12 and 24 months [12]. Knee pain will be assessed with the number rating scale (NRS) (range 0–10; optimal score is 0) at baseline, 3, 6, 12 and 24 months. Kinesiophobia will be measured with the Tampa scale at baseline (range 17–68; optimal score is 17), 12 and 24 months [14]. General quality of life will be measured with the EQ-5D-5L questionnaire (range − 0.329 to 1; optimal score is 1) at baseline, 3, 6, 12 and 24 months. EQ-5D-5L use is recommended for the assessment of quality of life in trauma patients, especially for economic assessments. The patients’ EQ-5D-5L health states will be converted into utility scores using the Dutch tariff. The EQ-5D will be used for the cost-utility analysis [15].

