### Data analysis

#### Primary outcome

In our primary analysis patients will be analysed according to their randomization group. To answer our primary research question, we will use linear mixed models to evaluate the between group difference in patients’ outcome as assessed by the IKDC questionnaire. The IKDC score after 24 months follow-up will be used as dependent variable. The randomized allocation will be used as an independent variable. We will adjust the analysis for potential confounders, namely baseline IKDC score. The used cluster (hospital) will be added as random factor into the model. The following model assumptions will be checked: linearity, homoscedasticity and normality of residuals.

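### The only IKDC course analysis described, a time-by-allocation interaction with baseline among the responses, gives no directional measure of faster recovery and handles baseline differently from the primary model

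*Protocol article*

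**What the plan says.** Under Objectives, the protocol article hypothesizes that with the algorithm "faster recovery of functional outcome will be achieved compared to the current practice". The Primary objective is narrower: being "superior to the current practice regarding recovery of functional outcome at two-year follow-up". The first Secondary objective covers the period up to then: being "superior to the current practice regarding recovery of functional outcome during two-year follow-up".

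Under Data analysis, Primary outcome, the 24-month IKDC is modelled with hospital as a random factor and baseline on the right-hand side: "We will adjust the analysis for potential confounders, namely baseline IKDC score".

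Under Data analysis, Secondary outcome, the group difference in the course of IKDC is to be judged "as indicated by the interaction between time point and randomized allocation", in a mixed model where "The IKDC score (at baseline and after 3, 6, 12 and 24 months of follow-up) will be used as a dependent variable". Allocation, follow-up and their interaction are the fixed terms. The section names no direction, early time point or summary over time. It labels secondary findings exploratory.

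The Secondary outcomes section lists IKDC measured for "ability to participate in sports activities at 3, 6 and 12 months follow-up with the IKDC questionnaire", and the Sample size section speaks of IKDC over several time points as change from baseline.

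**The concern.** Speed of recovery and superiority during follow-up are directional questions. The 24-month level cannot answer the first, since two arms can reach the same level at different speeds. The question therefore falls to the course model, whose stated indicator is an interaction over five visits. As a joint test on 4 degrees of freedom, this says only that the two curves are not parallel. A significant result could mean faster recovery, slower recovery or early harm.

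In addition, with baseline as a response and allocation free at baseline, each interaction coefficient is the group difference in change from baseline. The primary model instead adjusts for baseline. The report could then carry two 24-month IKDC differences, and in the course model an arm that starts lower by chance tends to look as if it recovers more.

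**Working it through.** The protocol gives no power or precision figure for the course analysis, so there is none to reproduce.

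**Inputs from the Sample size section.** SD 10.7 (reported for 24 months), ICC 0.10, 10 hospitals of 20 analysed patients, target difference 6 points.

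**Assumptions.** 5 hospitals per arm, the same SD at every visit, complete data, and equal between-visit correlation ρ = 0.5 (range 0.3 to 0.7) at hospital and patient level unless stated. The document gives no correlation. Power uses normal and chi-square references, which flatters every figure with only 10 hospitals.

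**Step 1: variance of the arm difference at one visit.** V = 10.7² × 2 × (1 + 19 × 0.10) / 100 = 114.49 × 2 × 2.9 / 100 = 6.64, so the SE is 2.58.

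**Step 2: joint interaction test.** With equal correlation, the noncentrality is λ = S / [V(1 − ρ)]. S is the sum of squares, about their mean, of the five gaps (0 at baseline, then months 3, 6, 12 and 24). For gaps 0, 6, 6, 3, 0 the mean is 3 and S = 9 + 9 + 9 + 0 + 9 = 36, so λ = 36 / (6.64 × 0.5) = 10.8.

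| Gaps at 3/6/12/24 months | S | λ | Power, 4 df (ρ 0.3 to 0.7) |
|---|---|---|---|
| +6/+6/+3/0 (faster) | 36 | 10.8 | 76% (59 to 94%) |
| 0/+3/+6/+6 (slower) | 36 | 10.8 | 76% (59 to 94%) |
| −6/−6/−3/0 (early harm) | 36 | 10.8 | 76% (59 to 94%) |

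The tie between the faster pattern and its mirror image holds under any covariance. The tie with the slower pattern depends on equal correlation.

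**Step 3: an early directional contrast.** The baseline-adjusted mean of the 3- and 6-month differences estimates +6.0, +1.5 and −6.0 for the three patterns. Power for the faster pattern is 91% (88 to 97%).

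**Step 4: a time-averaged contrast.** The area under the curve over months 3 to 24, by trapezoids, has weights 1.5, 4.5, 9 and 6 over 21.
- Faster: (9 + 27 + 27 + 0) / 21 = 3.0, power about 45%.
- Slower: (0 + 13.5 + 54 + 36) / 21 = 4.9, power about 85%.

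This contrast measures overall benefit and can favour the slower pattern.

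**Step 5: baseline handling at 24 months.**
- Change contrast: SE = √[2(1 − ρ)V] = 2.58.
- Adjusted contrast: SE = √[(1 − ρ²)V] = 2.23.
- Variance ratio: (2.58 / 2.23)² = 1.33.
- SD of the difference between the two estimates: (1 − ρ) × 2.58 = 1.3 points (0.8 to 1.8), against the 6-point target.

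Now let hospital-level (rc) and patient-level (re) correlations differ, with adjustment slope b = re. The ratio is [0.1 × 2(1 − rc)/5 + 0.9 × 2(1 − re)/100] / [0.1(1 + b² − 2b·rc)/5 + 0.9(1 − re²)/100].
- rc = re = 0.5: 0.029 / 0.02175 = 1.33.
- rc and re each 0.3 or 0.5: 1.33 to 1.54.
- rc = 0.9: 0.87 (re = 0.3) and 0.95 (re = 0.5), so the order reverses.

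**Step 6: constant +6 at every follow-up.** With baseline among the responses, the interaction has 65% power (48 to 88%). With months 3 to 24 only, the gaps are parallel, λ = 0, and the interaction rejects at its 5% level.

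**The case against.** The strongest reply is that the text never says joint test. With follow-up as a factor, the same model yields four signed differences in change, at 3, 6, 12 and 24 months, and choosing among them is commonly left to an analysis plan that is not shown here. This stands as a limit on severity. It does not remove the point, because the article itself fixes the interaction as the indicator and attaches no direction to it.

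Second, the Sample size section places the primary research hypothesis at 24 months, and secondary findings are exploratory. That also stands. A reader might infer that the trial's main hypothesis goes untested; the documents do not support this, since the 24-month analysis is specified and matches the primary objective.

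Third, a reader might infer that the two models contradict each other, or that baseline among the responses is an error. Neither follows. Both methods are accepted and serve different questions here. They target the same effect if baseline means are equal in expectation. The change-from-baseline form also agrees with the wording in the Sample size section.

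Fourth, the joint test is not weak in general: for the faster pattern its 76% exceeds the 45% of a time-averaged contrast. The case against it is its lack of direction.

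**Conclusion.** The point holds in a limited form. The course analysis as described has no directional measure of faster recovery, and it treats baseline differently from the primary model.

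A joint reading cannot separate faster recovery from early harm, nor, under equal correlation, from the slower pattern examined. The visit contrasts have 1.33 to 1.54 times the variance of adjusted ones at correlations of 0.3 to 0.5. The 24-month estimates from the two models would differ with an SD of about 1.3 points (0.8 to 1.8).

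All correlations, the equal SD over visits and the even split of hospitals are assumptions. If hospital effects are almost constant over time, the precision argument reverses slightly; the argument about direction does not depend on it. As the analysis is secondary and exploratory, this is a worthwhile improvement of low to moderate weight and no threat to the primary result.

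**What to change.** Keep the 24-month primary analysis as it is. For the course model:

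1. Use IKDC at 3, 6, 12 and 24 months as responses, with baseline IKDC as covariate (overall and by visit) and hospital and patient as random factors.
2. Report the signed group difference with its confidence interval at each visit.
3. Name one early baseline-adjusted contrast, for example the mean of the 3- and 6-month differences, as the measure of faster recovery. Read it beside the visit-by-visit differences, because a constant benefit also makes it positive.
4. If a time-averaged difference over 3 to 24 months is wanted, report it as overall benefit during follow-up and not as a test of speed.
5. Do not keep the interaction as the only test once baseline leaves the responses, since it would then miss a constant benefit.

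The cost is wording: IKDC is already scheduled at all five time points in Table 1. The one downside is a small loss of precision against unadjusted change if the hospital-level correlation over time is about 0.9 (variance ratio 0.87 to 0.95).

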### Cost effectiveness analysis

An economic evaluation will be conducted from a societal perspective in accordance with the Dutch guidelines [20] in which medical costs and loss of productivity costs will be considered. The time horizon will be 2 years to include all relevant costs and effects.

Both cost-utility (CUA) and cost-effective (CEA) analysis will be executed. Direct intramural and extramural care costs will be calculated (e.g. operation, physiotherapy, hospital days, costs of side effects, wound infections) and indirect non-medical costs (e.g. productivity losses). Data on medical resource use will be collected from the electronic hospital information systems, based on the iMTA Medical Consumption Questionnaire (iMCQ). Productivity costs are assumed to be substantial and will be registered in detail by the iPCQ. See Table 1 for follow-up moments regarding these questionnaires.

Healthcare costs will be analyzed conform to charges published in Dutch guidelines as they are most representative for the real healthcare costs [20]. The unit price of the ACL reconstruction and the intensive exercise program will be calculated, per individual center, with the micro-costing method.

The economic evaluation of the ACL treatment algorithm for patients with an ACL rupture compared to usual care will be calculated as the incremental cost-effectiveness ratio (ICER). The change in recovery of physical functioning, as assessed by the IKDC, will be the primary effect outcome measure for the CEA and quality adjusted life years (QALY) for the CUA. QALYs will be calculated for a 2 year period, according to the Dutch tariff for the EQ-5D.

In order to account for the possible clustering of data, analyses will be performed using linear multilevel analyses [21]. Accounting for the possible clustering of data (e.g., at the hospital level) is of great importance, as most economic evaluations fail to do so, whereas ignoring the possible clustering of data might lead to inaccurate levels of uncertainty and inaccurate point estimates.

The stability of the results to changes in costs and effect parameters will be measured with a sensitivity analysis. We will use bootstrapping with 5000 replications to determine 95% confidence intervals around the uncertainty surrounding ICERs and cost differences. Cost effectiveness planes and acceptability curves will be graphically presented using the net benefit framework [22]. Cost-effectiveness acceptability curves show the probability that the intervention is cost-effective in comparison with usual care for a range of different ceiling ratios thereby showing decision uncertainty. Discounting is not necessary for the time horizon of 24 months.

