Intramural and extramural medical costs will be assessed with the Medical Consumption Questionnaire (iMCQ) and productivity loss will be assessed with the Production Consumption Questionnaire (iPCQ) at 3, 6, 12, and 24 months follow-up. These questionnaires are validated by the Institute of Medical Technology Assessment (Erasmus University, Rotterdam, The Netherlands). iMCQ includes details on medical specialist care, physical therapy, hospitalization, nursing home, home care, and other costs directly associated with diagnosis, treatment and rehabilitation. iPCQ includes details on work resumption and production losses [16].

For patients, the efficacy of the shared decision making process will be evaluated using the score on the 9-ltem Shared Decision Making Questionnaire (SDM-Q-9) that is administered directly after the consultation. The SDM-Q-9 is a patient-reported measure that focuses on the decisional process by rating physicians’ and patients’ behavior in medical encounters [17]. The aggregated scores over all items of the SMD-Q-9 lead to a total raw score between 0 and 45, with 0 indicating the lowest and 45 indicating the highest level of perceived shared decision making.

For physicians, the efficacy of the shared decision making process will be evaluated at one or two time points, at the start of the inclusion period prior to the first inclusion in intervention and control centers and at the end of the inclusion period after the last inclusion in intervention centers. This will be evaluated using interviews/focus groups. The proposed topic lists are based on the SDM-Q-9-Doc questionnaire (the physician version of the SDM-Q-9) and the Technology Acceptance Model (TAM) [18]. Every interview/focus group session will be analyzed qualitatively and compared between control and intervention centers. After the inclusion period, we will analyze whether there is an improvement of perceived shared decision making when using our treatment algorithm.

Physical examination of the knee will be assessed by the objective IKDC questionnaire at baseline, 12 and 24 months. (Table 2) Information about the received treatment is reported including the surgeons fidelity to the intervention. We address the number of patients that cross over from their allocated treatment. (Serious) Adverse events ((S)AE’s) are noted.

**Table 2 Tab2:** Measurements per follow up moment

	*Baseline*	*3 months*	*6 months*	*12 months*	*24 months*
*Physical examination*	*x*			*x*	*x*

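### The plan rules out discounting over a 24-month horizon, so second-year costs, and second-year QALYs in the cost-utility analysis, count at face value

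*Protocol article*

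**What the plan says.** All but one of the relevant statements are in the Cost effectiveness analysis section of the protocol article.

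- Horizon: "The time horizon will be 2 years to include all relevant costs and effects".
- Effects in the cost-utility analysis (CUA): "QALYs will be calculated for a 2 year period, according to the Dutch tariff for the EQ-5D". The cost-effectiveness analysis (CEA) uses the change in IKDC as its effect measure instead.
- Framework: "An economic evaluation will be conducted from a societal perspective in accordance with the Dutch guidelines".
- Discounting: "Discounting is not necessary for the time horizon of 24 months". No reason and no rate are given, and discounting is mentioned nowhere else in the article.
- Sensitivity analysis: "The stability of the results to changes in costs and effect parameters will be measured with a sensitivity analysis". No discount rate is named among the parameters to be varied.

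The Secondary outcomes section confirms that second-year resource data will exist: "productivity loss will be assessed with the Production Consumption Questionnaire (iPCQ) at 3, 6, 12, and 24 months follow-up". Medical consumption is collected on the same schedule.

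**The concern.** A two-year horizon contains a full second year. Discounting adjusts for time preference, and the general convention is to apply it to whatever falls after the first 12 months. The sentence would be unremarkable for a one-year evaluation; for this one it fixes a rate of 0% for months 13 to 24.

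This is a stated analytic choice. It is not a detail that a condensed article leaves to a fuller document.

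At stake are the reported total costs, the cost difference, the QALY totals and the ICER, and how well they can be compared with evaluations that do discount.

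**Working it through.** The plan states no discounted figure, rate or expected ICER, so there is nothing of its own to reproduce. The check asks how far discounting could move the results.

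**Inputs from the article.** Horizon 2 years; QALYs over 2 years; cost questionnaires at 3, 6, 12 and 24 months; second-year weight under the plan 1.000.

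**Assumptions (not in the article).** Annual rate r from 1.5% to 5%. Year 1 is undiscounted and all of year 2 is discounted by one year. The share of the incremental cost falling in year 2 is s = 0.10 to 0.75. The share of the incremental QALYs falling in year 2 is t = 0.25 to 0.75.

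**Step 1: effect on second-year amounts.** Weight = 1/(1+r); reduction = 1 − 1/(1+r).

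- r = 1.5%: weight 0.985, reduction 1.5%
- r = 3%: weight 0.971, reduction 2.9%
- r = 4%: weight 0.962, reduction 3.8%
- r = 5%: weight 0.952, reduction 4.8%

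**Step 2: effect on the CUA ratio.** With rate rc for costs and re for effects, and with the yearly increments of the same sign,

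discounted ICER / undiscounted ICER = [(1 − s) + s/(1 + rc)] / [(1 − t) + t/(1 + re)].

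The rate pairs tried were equal rates of 1.5%, 3%, 4% and 5%, and one unequal pair (4% for costs, 1.5% for effects).

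- Lowest ratio: rc = 4%, re = 1.5%, s = 0.75, t = 0.25. Numerator 0.25 + 0.75 × 0.9615 = 0.9712; denominator 0.75 + 0.25 × 0.9852 = 0.9963; ratio 0.9748, a shift of −2.5%.
- Highest ratio: rc = re = 5%, s = 0.10, t = 0.75. Numerator 0.90 + 0.10 × 0.9524 = 0.9952; denominator 0.25 + 0.75 × 0.9524 = 0.9643; ratio 1.0321, a shift of +3.2%.
- No shift: one rate for both and s = t. At 4% with s = t = 0.5, the ratio is 0.9808/0.9808 = 1.

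**Step 3: effect on the CEA ratio.** Only the cost numerator changes, so the ratio is (1 − s) + s/(1 + r). It runs from 0.9985 (s = 0.10, r = 1.5%) to 0.9643 (s = 0.75, r = 5%), a shift of about −0.1% to −3.6%.

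**Step 4: yearly increments of opposite sign.** A net difference near zero can change sign. An illustration, not a forecast: +1000 in year 1 and −1020 in year 2 total −20 undiscounted. At 3% the total is 1000 − 1020/1.03 = +9.7; at 4% it is 1000 − 1020/1.04 = +19.2.

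**The case against.** Four things can be said for the plan.

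**The yardstick lies outside the article.** The only authority named is the Dutch guideline, whose text is not at hand. A reader might infer that the sentence breaches that guideline. The article cannot show this, and the point does not rest on it. It rests on the general convention of discounting beyond the first year, which the plan sets aside without a reason. What stands of the objection is that the fix cannot presume that the guideline prescribes a rate.

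**No direction can be shown.** A reader might infer that full weighting of the second year favours the algorithm, because usual care is expected to involve more delayed surgery and a second rehabilitation period. That would require delayed surgery to fall after month 12. The Background section defines delayed reconstruction as later than 3 months after trauma. It says only that half of the initially non-operative patients in two earlier trials were reconstructed within two years, without splitting year 1 from year 2. Operations in months 4 to 12 would not be discounted at all. This objection stands in full, so a bias between arms is not supported.

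**The reach is narrower than it looks.** QALY discounting concerns the CUA only. This also stands.

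**The size is small, and a place to check it exists.** A shift of a few percent in a secondary ratio, from 230 patients in ten hospitals and reported with bootstrap intervals, is unlikely to change a conclusion. In the sign-change illustration the net difference is near zero, so its sign would be uncertain anyway. The planned sensitivity analysis could hold a discounted scenario. It does not name one, however, and bootstrapping addresses sampling uncertainty rather than a fixed weighting rule.

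**Conclusion.** The point holds as a minor one. The article declares discounting unnecessary for a horizon that includes a full second year, so second-year costs (CEA and CUA) and second-year QALYs (CUA only) are taken at face value.

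The 1.5% to 4.8% reduction in second-year amounts depends on the assumed rates. The typical ICER shift of about 3% or less depends also on the assumed second-year shares and on yearly increments of the same sign; the largest value at the extreme of the assumed ranges was 3.6%, in the CEA. The direction is not established, and the shift may be zero.

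The primary IKDC comparison at 24 months is untouched.

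**What to change.** Replace the sentence on discounting with a rule that second-year costs and second-year QALYs are discounted in the base case. Use the rates of the guideline the plan says it follows, if that guideline sets them; otherwise use a prespecified rate, stated before the economic data are analysed. Add the undiscounted result to the sensitivity analysis already planned.

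The cost is one sentence and one line of code. No new data are needed, since the questionnaires at 12 and 24 months already separate the two years. The only downside is one extra reported result and slightly different totals.
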